##### 2.4.2.3 Functional near infrared spectroscopy

Participants complete an executive function task (Stroop) while being monitored by fNIRS at all-time points, using the Brite23 system from Artinis. The experimental setup consists of 23 sensors (optodes) placed over the prefrontal cortex and driven by a wireless device. Note that the Stroop task differs from the one used for neuropsychological testing as it is optimized for neuroimaging. During this version of the fNIRS Stroop task (10 min), the participants will be asked to identify either the color or the meaning of words as fast as they can. The trials will be categorized as naming (the word is colored, and its spelling is not a color), inhibition (the word spells a color name and is displayed with a color not matching its meaning) and switching (alternation between color identification and word reading). Trials are grouped into blocks of 12 trials, with a presentation rate of 2.5 s. Before each block, an instruction is displayed to indicate the trial type. Each block is followed by 20 s of rest to allow a return to baseline. This testing session is comprised of 4 blocks of each type, for a total of 12 blocks. Neurovascular coupling is assessed during this session.

#### 2.4.3 Tertiary outcomes

##### 2.4.3.1 Physical condition

The cardiorespiratory fitness, body composition, balance, lower and upper limb muscular strength, as well as mobility of the participant, is assessed using standardized and validated methods. Cardiorespiratory fitness is assessed using a VO_2_ Peak test (Gayda et al., 2017) on an electro-mechanically braked bicycle ergometer (Ergoline 800S, Bitz, Germany). Subjects have to maintain a constant pedaling cadence between 60 and 80 revolutions per minute. The test begins after a 3-min warm-up phase at 20 W. Depending on age, sex, and cardiovascular status of the patient, initial workload is individualized and increased by 5–15 W every min until exhaustion. Strong verbal encouragement is given throughout the test. Gas analyzers will be calibrated before each test using a gas mixture of known concentration (15% O_2_ and 5% CO_2_) and ambient air. Participants breathe through a facemask connected to a turbine with low resistance. The turbine is calibrated before each test using a 3-L syringe at several flow rates. Electrocardiographic activity is monitored continuously using an ECG (Marquette, Missouri) and blood pressure is measured every 2 min using a sphygmomanometer. Cardiopulmonary recordings are made every four respiratory cycles during testing and then averaged over 15 s. The maximal exercise test is continued until one of the following criteria are reached: (A) A plateau of VO_2_ despite an increase of power, (B) an R.E.R > 1.1, (C) measured maximal heart rate attaining 95% of age-predicted maximal heart rate, (D) inability to maintain the cycling cadence, (E) subject exhaustion with cessation caused by fatigue and/or other clinical symptoms (dyspnea, abnormal BP responses, or ECG abnormalities that will require exercise cessation). The highest VO_2_ value reached during the exercise phase is considered as the VO_2_Peak, and peak power output is defined as the power output reached at the last fully completed stage.

A bioimpedance analysis using a Tanita system (model 418 C, Japan) is also performed to assess the *body composition* (e.g., total and trunk fat mass, total fat-free mass). *Balance* and *lower limb muscle* strength are assessed by a one-leg balance test and a Five-Time-Sit-to-Stand test, respectively. The *grip strength* is measured for both arms with the help of a hydraulic hand dynamometer. Finally, mobility is assessed using the 10-meter walk test and the Timed Up-and-Go performed at spontaneous and fast walking speeds. These mobility and functional tests are commonly used in a clinical setting and recommended by the Canadian Consortium on Neurodegeneration in Aging (Montero-Odasso et al., 2019). Finally, the amount of physical activity is also recorded using an accelerometry tracker (e.g., Actigraph) worn for 7 days at baseline, before the start of any study visit.

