#### 2.3.1 Arm 1—physical exercise intervention (aerobic and resistance exercises)

Participants follow a periodized exercise training program supervised by a certified kinesiologist (with a minimum of a bachelor’s degree). The physical training sessions last 60 min, starting with a 5–10-min warm-up, followed by aerobic and resistance exercises, and ending with a 5–10-min cool-down and stretching period. The aerobic exercises last between 25 and 35 min and are performed mostly on stationary bicycles (other devices used only when participants could not use the stationary bicycle included treadmill or elliptical). Both continuous and high-intensity interval training modalities will be used during the program. The kinesiologist gradually increases the aerobic exercise intensity (in power) throughout the training based on the participant’s feedback. Participants are monitored with a heart rate strap to match the moderate to vigorous intensity zone defined by the American College of Sports Medicine (ACSM) (64–95% of maximum heart rate (HRmax; extracted from the VO2max test), and perceived exertion between 12 and 17 on the 6–20 Borg scale according to training modality). When the exercise intensity is close to the lower bracket on the HRmax or Borg scale, the kinesiologist will propose an increase in power. After aerobic training, 15–20 min of resistance exercises (RE) are performed with a similar individualized progressive increase in intensity. The one maximal repetition (1RM) is assessed for each primary RE movement at baseline, at T6, and at the end of the program. RE intensities during the training are between 40 and 70% of 1RM, for six different types of exercises involving major muscle groups. Each resistance training session is comprised of only three types of exercises of three sets of 6–15 repetitions, with a perceived exertion between 5 and 8 to the 10 pts OMNI scale. The power (aerobic exercise) and load (RE) will be re-adjusted after the T6 evaluation if necessary.

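### The fitness-test stopping sentence contradicts loading to exhaustion and, if followed literally, can understate VO2peak, peak power and HRmax

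*Protocol article*

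**What the plan says.** Section 2.4.3.1 describes one incremental cycling test for all participants. On loading, it says "initial workload is individualized and increased by 5–15 W every min until exhaustion", and adds: "Strong verbal encouragement is given throughout the test". On ending the test, it says: "The maximal exercise test is continued until one of the following criteria are reached". Five criteria follow:

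- A: a VO2 plateau despite rising power
- B: RER above 1.1
- C: "measured maximal heart rate attaining 95% of age-predicted maximal heart rate"
- D: inability to keep the pedalling cadence
- E: "subject exhaustion with cessation caused by fatigue and/or other clinical symptoms", with dyspnoea, abnormal blood pressure responses and ECG abnormalities given as examples

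VO2peak is the highest VO2 reached during exercise, and "peak power output is defined as the power output reached at the last fully completed stage".

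The test also feeds the intervention. Section 2.3.1 sets the aerobic zone at 64–95% of "maximum heart rate (HRmax; extracted from the VO2max test", together with Borg 12–17, and the multidomain arm uses the same exercise programme (section 2.3.2). Section 2.3.3 caps the control arm at 64% of HRmax and Borg below 11. Table 2 schedules the test at baseline, 6 months and 12 months.

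**The concern.** The paragraph gives two incompatible instructions. One loads the participant to exhaustion. The other ends the test at the first of five criteria, two of which are not limits of the participant. D and E are real reasons to stop. A plateau (A) does not make the recorded value submaximal. B and C can both be met while the participant is still able to pedal, and C lies below the predicted maximum by construction.

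All three quantities taken from the test depend on when it ends: VO2peak, peak power and HRmax. A test stopped at B or C would enter a threshold value under a peak label. The first two are tertiary outcomes. HRmax sets the exercise zone and the control ceiling, and it prompts progression: "When the exercise intensity is close to the lower bracket on the HRmax or Borg scale, the kinesiologist will propose an increase in power". A low HRmax puts that lower limit at a lighter true intensity, so the prompt comes later than intended.

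**Working it through.** The plan gives no figure for this point, so there is none to reproduce. The check is of wording first, then illustrative arithmetic.

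**Wording.** The stopping sentence is disjunctive: any one criterion suffices. Setting the criteria against the instruction to load to exhaustion:

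| Criterion | Ends the test as written | Compatible with a maximal value |
|---|---|---|
| A plateau | yes | yes |
| B RER above 1.1 | yes | not necessarily |
| C 95% of predicted HR | yes | not necessarily |
| D loss of cadence | yes | yes |
| E exhaustion or symptoms | yes | yes if exhausted; otherwise a clinical stop |

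Only B and C create the conflict. No other section resolves it.

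**HRmax if C ends the test.** Inputs are 0.95 (criterion C) and the 64% and 95% limits (sections 2.3.1 and 2.3.3). Let r be true HRmax divided by age-predicted HRmax. The article does not give r, so it is assumed, from 0.95 to 1.10.

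Recorded/true HRmax = 0.95/r for r above 0.95. At r of 0.95 or below, C cannot cut the test short. A nominal limit of L% of recorded HRmax lies at L × 0.95/r of true HRmax.

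| r (assumed) | 0.95/r | HRmax understated by | 64% limit falls at | 95% limit falls at |
|---|---|---|---|---|
| 0.95 | 1.000 | 0% | 64.0% | 95.0% |
| 0.975 | 0.974 | 2.6% | 62.4% | 92.6% |
| 1.00 | 0.950 | 5.0% | 60.8% | 90.25% |
| 1.05 | 0.905 | 9.5% | 57.9% | 86.0% |
| 1.10 | 0.864 | 13.6% | 55.3% | 82.0% |

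The result does not depend on which age-prediction formula is used, because that formula enters only through r.

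**Peak power.** The step is 5–15 W per one-minute stage. Losing k completed stages lowers recorded peak power by k × 5 to k × 15 W: 5–15 W for k = 1 and 10–30 W for k = 2. The number of stages lost is assumed.

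**Not computable.** The article gives no basis for the VO2peak shortfall, the loss from stopping at B, or the share of tests that would end at B or C.

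**The case against.** The strongest reply is that the paragraph, read as a whole, already describes a test to exhaustion. The test is called maximal, the workload rises to exhaustion and participants are strongly encouraged. Criterion C speaks of a measured maximal heart rate, a quantity fully known only once the test is over, which suits an effort check better than a running stop signal. The section also cites a published method, and laboratory practice usually sits in a manual that is not shown here.

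Much of this stands. A merger of effort checks and stop reasons into one list is the likely explanation. But the article states a rule rather than leaving one out, and that rule contradicts the sentence on loading. An operator who follows it as printed may stop early.

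The reply is also right about consequences. Every HRmax percentage rests on an assumed r and is zero at r of 0.95 or below. In the exercise arms, power also follows participant feedback and the Borg range; in the control arm, the Borg ceiling applies too. The exercise floor and the control ceiling are both 64% of the same recorded quantity, so they shift in the same direction and separation of the arms is largely preserved.

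A reader might infer that tests in this trial are in fact being cut short, or that the arms are compared unfairly. The documents support neither. They do not report why any test ended. Section 2.4.3.1 describes a single test for everyone, and section 2.9 blinds the outcome assessors to allocation.

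**Conclusion.** The point holds as a minor one. The protocol contradicts itself on how the fitness test ends, and the literal rule can understate VO2peak, peak power and HRmax. If C ends the test, HRmax is 2.6% to 9.5% low for r between 0.975 and 1.05, and 5.0% low at r = 1. Each stage lost costs 5–15 W of peak power. These are conditional illustrations: they assume the sentence is followed literally, that C is met before exhaustion, and a value of r that the article does not supply.

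It would be tempting to conclude that the training dose is compromised, and with it the primary comparison. The text does not carry that far. Borg targets limit the effect on dose, the primary cognitive outcomes are not measured by this test, and no between-arm bias is shown.

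**What to change.** Reword the stopping sentence so that the test ends at exhaustion, inability to hold the cadence, or a clinical safety stop (D and E), and B and C are recorded only to classify a completed test as maximal. A may stay as it is.

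Table 1 gives October 2021 as the date of first enrolment, so some tests will already have been done. Flag VO2peak, peak power and HRmax as possibly submaximal for any test that ended at B or C, using the RER and heart-rate data those criteria already require. Keep flagged tests in the between-arm comparison: at 6 and 12 months the reason a test ended is a post-randomisation variable that training may affect, so excluding on it could introduce bias.

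The cost is one sentence and a data flag. If tests already run to exhaustion, nothing else changes. If not, some inactive participants over 60 with cardiovascular risk factors will have slightly longer maximal tests. The existing ECG and blood-pressure monitoring and the symptom stops in E must therefore remain in force.

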##### 2.4.3.2 Cardiovascular health

General medical data is collected at the first visit, and detailed medical data (including medical history) is collected during the dedicated appointment with a study physician. The number of cardiovascular risk factors is assessed based on the presence of hypertension, dyslipidemia, diabetes, obesity (i.e., waist circumference), active smoking (i.e., one cigarette or more per day), physical inactivity, and family history of premature CVD (i.e., before 45 years for men and 55 for women).

Peripheral endothelial function of the brachial artery: Flow-mediated dilation is quantified by measuring brachial artery blood velocity and diameter by ultrasound (uSmart3300, Terason) with a linear array transducer (5–12 MHz) prior to and following 5 min of forearm ischemia. All procedures are performed according to recent guidelines (Zeki et al., 2014).

Central artery stiffness: Carotid femoral pulse-wave velocity is measured according to recent American Heart Association guidelines (Townsend et al., 2015). Arterial blood pressure tracings are recorded continuously and simultaneously from the carotid and femoral arteries using a pencil tip tonometer. Using the foot of the pressure waveforms, transit time is determined by the delay in arrival of the pulse wave at the carotid and femoral measurement sites. The travel distance of the pulse wave is estimated from distances taken with a measuring tape on the body surface.

##### 2.4.3.3 Biological markers

In an exploratory manner, this trial will collect biological markers of stress, metabolic function, as well as neurotrophic and genetic markers, using diurnal salivary cortisol, blood samples and the gut microbiome. Due to the potentially uncomfortable procedure of collecting the gut microbiome this assessment is made optional.

The salivary diurnal *cortisol* secretion is sampled on three non-consecutive days, at the time of awakening, 30 min after, 60 min after, at 2:00 pm, 4:00 pm, and 9:00 pm. The participants use Salivettes (Sarstedt, Ville St-Laurent) to collect their saliva, and any relevant information related to their collection is reported in a logbook (e.g., time of awakening and bedtime, time of collection). The data collection, manipulation, and interpretation will be done according to the guidelines (Stalder et al., 2016).

A fasting *blood sample* is also collected from all participants to measure lipids profile, glucose, HbA1C, insulin, creatine, electrolytes, high-sensitive c-reactive protein, ApoB, plasma human BDNF concentration (by enzyme-linked immunosorbent assay). DNA and RNA extraction and sequencing are also planned (for future transcriptome investigations, and to generate high quality genome-wide genotyping data that include the APOE and BDNF genes). The blood draw is done fasting by a nurse in the morning.

Gut *microbiome* is assessed using fecal samples collected at baseline and at the end of the intervention (Koblinsky et al., 2023). The participants do the collection at home, after being instructed by a research assistant. The preparation and DNA extraction is done immediately after receiving the samples, then they will be stored at −80°C until further processing.

##### 2.4.3.4 Questionnaires

Validated self-reported questionnaires assess mood, anxiety, health profile, and health-related quality of life of participants. Participants fill the Perceived Stress Scale (Cohen et al., 1983), the Geriatric Depression Scale (Yesavage et al., 1982), the State-Trait Anxiety Inventory (Spielberger et al., 1970), the 12-item Short Form health-related quality of life survey (Ware et al., 1996), the Pittsburgh Sleep Quality Index (Buysse et al., 1989), the Short Diet Questionnaire (Gilsing et al., 2018), the Social and Community Involvement Questionnaire (Richard et al., 2009), the Physical Activity Scale for the Elderly (baseline only) (Washburn et al., 1993), the Short Form Bem Sex-Role Inventory (baseline only) (Bem, 1974), the long COVID symptom and impact questionnaire adapted from Tran et al. (2022) and WHO’s Global COVID-19 Clinical Platform (WHO, 2021). Cognitive reserve is also measured using years of education and a modified version of the Rami and colleagues’ cognitive reserve questionnaire (baseline only) (Rami et al., 2011) adapted for French and English by the CIMA-Q team (Belleville et al., 2019).

### 2.5 Participant timeline

First, a research team member performs the initial contact over the phone. During this call, the study structure is introduced, and a pre-screening of potential participants with no major physical or medical limitations to exercise is done. Interested individuals who meet these two main criteria are then assessed for eligibility. Immediately after the pre-screening call, the interested and eligible participants will receive the information and consent form (ICF). During a preliminary call, the ICF will be further explained in detail, and oral consent will be obtained. Following this, the participants will be screened for major physical limitations to exercises (PARQ +). After obtaining written consent, the cognitive (MMSE) screening will be performed with a research assistant. Individuals confirmed with no cognitive impairment will be considered enrolled. After the first visit, participants will have 1 week without any assessment or intervention training to collect accelerometer data at home under their usual conditions. They are also instructed to collect their biological samples during days when they do not have any research visits. After this is done, participants will return to continue the remaining assessments (see Table 1).

### 2.6 Sample size

A power and sample size analysis was performed by a biostatistician team independent of the study team, based on a previous meta-analysis comparing exercise training alone to combined physical and cognitive intervention on cognition (Zhu et al., 2016). Using an intent-to-treat principle with multiple imputations, a sample size of 42 subjects in each group will have 80% power to detect a group difference in means of −0.186 (the difference between a physical alone training mean of 0.239 and a combined training mean of 0.425, for an effect size of 0.624) assuming that the common standard deviation is 0.298 using a two group *t*-test with a 0.050 two-sided significance level. Taking into account a 20% attrition rate observed in our previous exercise studies, we will thus recruit 53 participants per intervention arm (53 × 3 arms), for a total of 159 participants. For the secondary outcome (neuroimaging), we based our calculation on the 2% increase in hippocampal volume following a 12-month physical exercise training reported by Erickson et al. (2011) (Erickson et al., 2011). Results suggest that 60 participants are needed to observe significant changes post-exercise. Since 2 arms involve exercise training in this study (total 106 participants), the numbers of participants are largely enough.

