The primary outcome will be the changes in cognitive performance (MoCA, processing speed, executive functions, and memory). Computerized cognitive tasks will be analyzed separately. We will perform four linear mixed-effects models analyses (for every cognitive measure) with intervention group as fixed factors and adjustments for relevant covariates. An unstructured covariance structure will be used to model the within-patient errors. The final selection of covariates will include age, sex, and education and any potential relevant demographic variable that show a group difference. These will consider, but not be limited to BMI, stress, mood, genetic risk, medical history, and CVRF. A Bonferroni correction will control for multiple comparisons with a significance level set at *p* < 0.0125. The same statistical model will apply for the brain imaging secondary outcomes: pulsatility, vasoreactivity and autoregulation indices, regional cerebral blood flow, grey matter volume and CSVD lesions (Bonferroni-corrected for number of regions). To inform potential future studies, exploratory analyses will also performed in which we will test if certain variable impact the effectiveness of the intervention on the primary (cognition) or secondary (imaging) variables. Due to the exploratory nature of those analyses, no multiple comparison correction will be made and no *a priori* power analysis is made. The exploratory analyses can include but not be limited to testing the mediating or moderating role of the available medical (including cardiovascular health, cardiovascular risk factors), psychological, and biological markers on the group effect. The mediating and moderating analyses will be performed according to the guidelines published by Hayes (2017).

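### The 80% power is computed at two-sided 0.05, but each primary outcome is tested at 0.0125, where 42 per arm give about 62% power

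*Protocol article*

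**What the plan says.** Section 2.6 of the Protocol article (Sample size) bases the trial size on the multidomain versus physical exercise comparison. The effect is "the difference between a physical alone training mean of 0.239 and a combined training mean of 0.425, for an effect size of 0.624". Both groups are taken to share an SD of 0.298. On that basis "a sample size of 42 subjects in each group will have 80% power to detect a group difference in means", by a two-group t-test "with a 0.050 two-sided significance level". Allowing for 20% attrition, this becomes 53 per arm and 159 in total.

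Section 2.12 (Statistical methods) then sets out the primary analysis. "The primary outcome will be the changes in cognitive performance (MoCA, processing speed, executive functions, and memory"), and "We will perform four linear mixed-effects models analyses (for every cognitive measure"). On the threshold it says: "A Bonferroni correction will control for multiple comparisons with a significance level set at *p* < 0.0125". That is 0.05/4, one share for each of the four measures. Sections 1.2 and 2.4.1 and Table 1 list the same four measures.

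Section 2.6 mentions neither the 0.0125 threshold nor the four outcomes.

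**The concern.** A power statement is useful only if it describes a test the trial will run. Section 2.6 assumes rejection at 0.05, whereas section 2.12 allows rejection only at 0.0125 for each primary measure. Sample size, difference and SD are unchanged between the two sections, so the stricter threshold must lower the power, and the article does not acknowledge the loss.

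This is a contradiction between two sections of the same document, both of which give explicit figures. An unseen analysis plan could not fill it in without changing one of the two.

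The 80% figure is the stated justification for 159 participants on the primary outcome. If it is too high, a non-significant result on, say, executive function will be read as stronger evidence against benefit than the design can supply.

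**Working it through.** **Inputs**

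| Quantity | Value | Source |
|---|---|---|
| Difference in means | 0.425 − 0.239 = 0.186 | 2.6 |
| Common SD | 0.298 | 2.6 |
| Evaluable per arm | 42 | 2.6 |
| Attrition | 20% | 2.6 |
| Recruited per arm | 53 (159 in total) | 2.6 |
| Alpha in the power calculation | 0.05, two-sided | 2.6 |
| Alpha in the primary analysis | 0.0125 (= 0.05/4) | 2.12 |

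**Method.** Two-sample t-test, noncentral t distribution, n per arm:

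- d = 0.186/0.298 = 0.624
- noncentrality λ = d × √(n/2)
- degrees of freedom = 2n − 2
- power = P(|T| > t crit), where T is noncentral t with parameter λ and t crit is the 1 − α/2 quantile of the central t

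**Step 1: reproduce the stated figure.** With n = 42, λ = 0.624 × √21 = 2.86 on 82 df. At α = 0.05, t crit = 1.989 and power = 80.7%. The smallest n reaching 80% is 42, and 42/0.8 = 52.5, rounded up to 53 per arm, or 159 in total. The calculation in section 2.6 reproduces.

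**Step 2: change only alpha.** With λ still 2.86 and α = 0.0125, t crit = 2.554 and power = 62.1%. The normal approximation gives 64.2%. The chance of missing the assumed effect on a given outcome is 1 − 0.621 = 0.379.

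**Step 3: best case on attrition.** If all 53 per arm contributed complete data, λ = 0.624 × √26.5 = 3.21 on 104 df, t crit = 2.542 and power = 74.8%. Full retention still falls short of 80%.

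**Step 4: what 80% would need at 0.0125.**

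- Sample size: 58 per arm gives 79.3% and 59 gives 80.1%, so 59 evaluable. 59/0.8 = 73.75, so 74 recruited per arm and 3 × 74 = 222 in total.
- Effect size at 42 per arm: d = 0.743, and 0.743 × 0.298 = 0.221, against the assumed 0.186.

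| Evaluable per arm | α = 0.05 | α = 0.0125 |
|---|---|---|
| 42 | 80.7% | 62.1% |
| 53 | 88.9% | 74.8% |
| 59 | 92.0% | 80.1% |

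**Step 5: a stricter reading.** The primary hypothesis in section 1.2 compares the multidomain arm with both exercise and active control. If alpha were also divided over those two comparisons, it would be 0.0125/2 = 0.00625 and power with 42 per arm would be 52.4%. The 62.1% therefore uses the more favourable reading.

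**The case against.** Four points can be made for the plan.

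*The planned analysis is not an unadjusted t-test.* Section 2.12 specifies mixed models with an unstructured covariance, adjusted for age, sex and education. Adjustment can reduce residual variance. As an illustration only, if covariates correlated with the outcome at r, the effective d would be 0.624/√(1 − r²). Power at 0.0125 with 42 per arm would then be about 67% for r = 0.3, 71% for 0.4, 77% for 0.5 and 84% for 0.6; 80% needs r of about 0.54. This stands as a caution against treating 62% as the power of the mixed model. It does not rescue the 80%: the article gives no correlation, claims no gain, and does not say whether the SD of 0.298 is for raw or change scores, so some of the gain may already be counted.

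*Multiple imputation keeps everyone in the analysis.* Participants who drop out after the 6-month visit do contribute some information, so 42 is the pessimistic end. Imputation cannot do better than complete data on all 53, however, and that gives 74.8%.

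*There are four chances to succeed.* If the assumed effect were present on all four outcomes, the chance of at least one rejection would be well above 62%: about 93% to 83% in simulation with assumed correlations between outcomes of 0.3 to 0.7. So the concern about over-reading a null result applies to a single measure, not to a null result across all four. The article does not define success as any one of four, nor does it power for that.

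*The arithmetic in section 2.6 is right, and type I error is protected.* Both are true. The fault is an inconsistency between sections, and no estimate is biased by it.

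**Conclusion.** The point holds: the power statement is wrong as written for the primary analysis the article prescribes. Per outcome, for multidomain versus exercise, under the protocol's own difference, SD and unadjusted t-test, power at 0.0125 is 62.1% with 42 per arm and 74.8% with 53. Under those assumptions, neither end of the retention range reaches the stated 80%. The probability of missing the assumed effect on a given measure at 42 per arm is about 38%, nearly double the 20% implied.

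The mixed models might narrow this gap, but by an amount the article gives no means of judging. The statement should be corrected because it is the stated basis for the recruitment target on the primary outcome.

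**What to change.** Restate the power in section 2.6 at the level section 2.12 uses, and label what it refers to. Suggested wording: 'For each primary outcome, comparing multidomain with physical exercise by an unadjusted two-group t-test at two-sided alpha 0.0125, 42 evaluable participants per arm give about 62% power for a standardised difference of 0.624 (difference 0.186). Power is 80% for a standardised difference of about 0.74 (difference 0.221).' If the sponsor wishes to credit the mixed model with a gain, the assumed correlation and its basis should be stated alongside.

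Keep the enrolment target, the outcomes, the 0.0125 threshold and the analysis model as they are. The cost is one paragraph in the protocol, and the matching text in the analysis plan if it repeats the statement. The stated power becomes less favourable; no extra participants are needed.

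Two larger alternatives would also remove the contradiction: naming a single primary outcome tested at 0.05, or enlarging the trial to 74 per arm (222 in total). Either changes the design, and neither is needed to make the document accurate.
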